## 4.2 Data quality and blind review

Data quality checks will initially be conducted in REDCap. Range checks will be performed for each variable at each time point. The following tasks will be conducted blinded to group allocation: 1) Missing and out of range data in REDCap will be checked against paper data collection forms to confirm values and corrected in REDCap; 2) activPAL data will be cleaned and corrected in REDCap as outlined in appendix 2; 3) replacement of missing data for participants unable to perform the test task as outlined in appendix 1.

Once this process is complete and continuing using a blinded review range checks will be performed for each variable at each time point and histograms will be visually inspected for each variable at each time point using stata. The distribution of continuous variables will be evaluated to inform whether change scores will be used for analysis.

## 4.3 Activity (primary outcome)

## The time spent upright (minutes per day averaged over days worn), assessed using the activPAL activity monitor will be treated as a continuous variable. The effect of group allocation on the outcomes at 6-month follow-up will be analysed using linear regression models with baseline scores entered into the linear regression models as covariates. Or if distributions are overly skewed (on visual inspection of histograms) the change scores (post-pre) will be analysed.

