## 4.1 Analysis principles

• Data will be coded to permit blinding to group allocation in the analysis of primary outcomes.

• The primary analyses will be conducted in accordance with the intention-to-treat principle.

• All tests are two-sided and the nominal level of α will be 5%.

• All statistical analyses will be adjusted for baseline scores for that variable (except WHODAS and IPEQ for which baseline scores were not measured) but no other variables except where indicated. Sensitivity analysis will be conducted not adjusting for baseline scores for the coprimary outcomes only.

• Subgroup analyses will be pre-specified and outlined below. These will be carried out irrespective of whether there is a significant treatment effect on the primary outcome.

• Where data are missing due to loss to follow up, we will report the number of observations; we will not impute missing values for the primary analyses. Sensitivity analysis may be conducted for the primary outcomes using multiple imputation of missing data if more than 10% of outcome data are missing.

• P-values will not be adjusted for multiplicity. A significant effect must be observed on both co-primary endpoints to declare the intervention effective. However, the outcomes and time points are clearly categorised by degree of importance (primary and secondary) and a limited number of subgroup analyses will be pre-specified.

• Descriptive statistics will include numbers and percentages of participants with specific scores or means and standard deviations in each group at baseline and follow-up.

##

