## 4.4 Mobility (primary outcome)

The primary analyses will be conducted using linear models with baseline scores entered as a covariate. The groups will be compared on 6-month assessment scores. The primary analysis will use the CSPS^1^ This is the continuously scored version of the Short Physical Performance Battery^2^ and gives a composite score between 0 and 3 based on timed performance of three mobility tasks: the ability to stand for up to 10 sec with feet in different positions (together, side by side, semi-tandem and tandem), 4-metre walk and time to rise from a chair five times.

The primary analysis will be adjusted only for baseline scores. A secondary adjusted analysis will be conducted adjusting for the stratification factors of study site and health condition (whether or not the person has a neurological condition that affects daily activities). Further adjusted analyses will be conducted if major imbalances between the groups at baseline are observed.

If outliers are present in the data or the model assumptions are grossly violated after treatment is included in the model, some sensitivity analyses based on robust regression will be conducted.

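### Switching co-primary upright time to change scores when histograms look skewed is an unreliable remedy that can cost precision and never gains any

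*SAP*

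**What the plan says.** Section 4.3 sets the default for upright time: "The effect of group allocation on the outcomes at 6-month follow-up will be analysed using linear regression models with baseline scores entered" as covariates. It then gives the alternative: "Or if distributions are overly skewed (on visual inspection of histograms) the change scores (post-pre) will be analysed". Section 4.5 uses the same sentence for the remaining continuous secondary outcomes.

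Section 4.2 places the decision in the blinded data review: "The distribution of continuous variables will be evaluated to inform whether change scores will be used for analysis". What is inspected is therefore the variables themselves, not model residuals, and no degree of skewness is named.

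Three other statements bear on this:

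- Section 4.1 states the general rule, "All statistical analyses will be adjusted for baseline scores for that variable", with an exception: "except WHODAS and IPEQ for which baseline scores were not measured". It does not say whether the rule carries over to a change-score analysis.
- Section 4.1 also sets the success criterion: "A significant effect must be observed on both co-primary endpoints to declare the intervention effective".
- Section 4.4 deals with outliers and grossly violated assumptions for the other co-primary, mobility, without changing its primary model: "some sensitivity analyses based on robust regression will be conducted". Section 4.3 has no such provision for upright time.

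**The concern.** The trigger looks at the wrong thing. Linear regression assumes nothing about the shape of the raw outcome. Only the residuals matter, and chiefly in small samples.

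The remedy is also doubtful. Subtracting baseline is not a transformation towards symmetry. It replaces the estimated baseline slope by a slope fixed at 1. Whether that makes the distribution more symmetric depends on how the baseline and follow-up distributions compare.

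At stake is the precision of one co-primary comparison in a trial that needs both to be significant. A second issue is that the primary model is left open to a visual judgement without a stated criterion.

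**Working it through.** **Inputs.** From the SAP: the default model and the fallback (4.3), the timing and basis of the choice (4.2), and a two-sided 5% level (4.1). The SAP gives no sample size, power, SD or baseline–follow-up correlation, so there is no figure to reproduce. All values of r, k, power, sample size and distribution below are assumptions.

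**1. Precision if the change score is analysed without baseline.** Set the follow-up SD to 1 and the baseline SD to k.

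- Variance of the change score: 1 + k² − 2rk.
- Residual variance of baseline-adjusted regression (ANCOVA): 1 − r².
- The difference is (k − r)², so the ratio is 1 + (k − r)²/(1 − r²). At k = 1 this reduces to 2/(1 + r).

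| k | r = 0.3 | r = 0.5 | r = 0.7 |
|---|---|---|---|
| 0.5 | 1 + 0.04/0.91 = 1.04 | 1 + 0/0.75 = 1.00 | 1 + 0.04/0.51 = 1.08 |
| 1 | 1 + 0.49/0.91 = 1.54 | 1 + 0.25/0.75 = 1.33 | 1 + 0.09/0.51 = 1.18 |
| 1.25 | 1 + 0.9025/0.91 = 1.99 | 1 + 0.5625/0.75 = 1.75 | 1 + 0.3025/0.51 = 1.59 |

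The added term is a square, so the ratio is never below 1. It equals 1 only when k = r.

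**2. Power.** If ANCOVA had 80% power (assumed), power with change scores is Φ(2.80/√ratio − 1.96).

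- k = 1: 62%, 68% and 73% at r = 0.3, 0.5 and 0.7.
- k = 0.5, r = 0.7: 2.80/√1.08 − 1.96 = 0.73, so about 77%.
- k = 1.25, r = 0.3: 2.80/√1.99 − 1.96 = 0.02, so about 51%.

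**3. Does subtraction remove skewness?** Simulated log-normal pairs, with log-scale correlations of 0.3, 0.5 and 0.7:

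| Scenario | Follow-up skewness | Change-score skewness | Variance ratio to ANCOVA |
|---|---|---|---|
| Identical distributions (log-SD 0.6) | 2.2 to 2.3 | about 0 | 1.21 to 1.58 |
| Baseline lower and less variable (k about 0.45) | 2.3 | 1.8 to 2.4 | 1.00 to 1.08 |
| Baseline mildly skewed (0.95; k about 0.12) | 2.8 to 2.9 | 3.0 to 3.1 | 1.02 to 1.49 |

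Subtraction cancels the skewness when the two distributions match, and there it costs precision. When they differ, most or all of the skewness remains, and it can be slightly worse.

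**4. Is the switch needed?** In 4,000 simulated trials of 200 patients with log-normal data and no effect, ANCOVA rejected in 4.8% against a nominal 5%. With an effect added, identical distributions and log-scale correlation 0.5, the empirical standard error was 14.3 for ANCOVA and 17.0 for change, with power 78% against 65%. With k about 0.45 the powers were practically equal (53.5% and 53.3%).

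**5. If baseline is kept in the change-score model.** Regressing (follow-up − baseline) on group and baseline changes only the baseline coefficient, by −1. The treatment estimate and residuals are those of ANCOVA. In simulation the estimates differed by less than 1e-12. On this reading the switch loses nothing and cannot reduce skewness.

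**The case against.** **The precision loss may be nil.** Baseline is taken in people admitted to inpatient rehabilitation and the outcome at 6 months, so equal SDs cannot be assumed. A reader might take the 62% to 73% power as the expected cost. The SAP does not support that: those figures belong to k = 1, and at k = 0.5 the loss is close to zero. This stands, and it is why only a range can be given.

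**Change scores can help with skewness.** True when baseline and follow-up distributions are alike, where ANCOVA residuals stayed skewed (1.8 to 2.2) and the change score did not. But ANCOVA held its level in that setting with 200 patients, so the symmetry was bought with precision and was not needed for validity. A reader might also infer that failure to cure skewness and loss of precision always go together. They need not: in the second scenario the skewness stayed but almost no precision was lost.

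**The choice is blinded.** A visual, threshold-free rule invites the inference that the model could be picked for its result. Sections 4.1 and 4.2 do not support this, since the review and the primary analyses are done masked to group. Under randomisation the unadjusted change-score estimate is also unbiased. Over-correction of a chance baseline imbalance when the true slope is below 1 is a conditional weakness, not a bias of the procedure.

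**Section 4.1 may already require baseline in the model.** It is tempting to call section 4.3 a contradiction of 4.1. But 4.3 does not say that the covariate is dropped, so the text is ambiguous rather than contradictory. If 4.1 governs, the fallback is merely redundant.

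**WHODAS and IPEQ.** Section 4.5 puts self-reported activity and participation under baseline adjustment or change scores, although neither instrument had a baseline. A reader might conclude that they cannot be analysed. Section 4.1 exempts both, so an unadjusted follow-up comparison is available. What remains is a wording inconsistency.

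**Conclusion.** The point holds as one of efficiency and unsuitable method. The switch is triggered by raw histograms, which is not what the model depends on, and its remedy for skewness is unreliable.

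If baseline is dropped, the variance is between 1.00 and 1.99 times that of ANCOVA over the assumed grid (r 0.3 to 0.7, k 0.5 to 1.25): from no loss to a substantial one, and asymptotically never a gain. If baseline is kept, the fallback has no effect on the treatment estimate. On neither reading does it improve precision. The size cannot be narrowed without r and k, which the SAP does not give.

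The type I error and the integrity of the blinded choice are not in question. The passage should be corrected because it concerns a co-primary and the change costs almost nothing, but it does not undermine the analysis.

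**What to change.** - Delete the change-score fallback from sections 4.2, 4.3 and 4.5.
- State that the follow-up score regressed on group and baseline is the fixed primary model for upright time.
- If residuals are clearly non-normal, report bootstrap or heteroscedasticity-robust confidence intervals for that same model.
- Extend the robust-regression sensitivity analysis of section 4.4 to upright time.
- Align section 4.5 with 4.1 by stating that WHODAS and IPEQ are compared at follow-up without own-baseline adjustment and without change scores.

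The cost is SAP wording only. No new data are needed.

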## 4.4 Mobility (primary outcome)

The primary analyses will be conducted using linear models with baseline scores entered as a covariate. The groups will be compared on 6-month assessment scores. The primary analysis will use the CSPS^1^ This is the continuously scored version of the Short Physical Performance Battery^2^ and gives a composite score between 0 and 3 based on timed performance of three mobility tasks: the ability to stand for up to 10 sec with feet in different positions (together, side by side, semi-tandem and tandem), 4-metre walk and time to rise from a chair five times.

The primary analysis will be adjusted only for baseline scores. A secondary adjusted analysis will be conducted adjusting for the stratification factors of study site and health condition (whether or not the person has a neurological condition that affects daily activities). Further adjusted analyses will be conducted if major imbalances between the groups at baseline are observed.

If outliers are present in the data or the model assumptions are grossly violated after treatment is included in the model, some sensitivity analyses based on robust regression will be conducted.

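### Both co-primary models omit the factors used to stratify randomisation, which costs precision to the extent that those factors predict the 6-month outcome beyond baseline

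*SAP*

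**What the plan says.** - **General rule (SAP 4.1).** Analyses adjust for the baseline value of the outcome, "but no other variables except where indicated". Tests are two-sided at 5%. The intervention is declared effective only if both co-primary endpoints are significant.
- **Upright time (SAP 4.3).** The 6-month outcome "will be analysed using linear regression models with baseline scores entered into the linear regression models as covariates". The fallback for skewed data is: "Or if distributions are overly skewed (on visual inspection of histograms) the change scores (post-pre) will be analysed". Neither sentence mentions the strata, and no strata-adjusted analysis follows.
- **Mobility (SAP 4.4).** "The primary analysis will be adjusted only for baseline scores". The next sentence gives the strata a supporting role: "A secondary adjusted analysis will be conducted adjusting for the stratification factors of study site and health condition".
- **Subgroups (SAP 4.6).** Neurological condition and State appear as interaction tests. This does not bring the strata into the primary estimate of the treatment effect.

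The SAP does not give the sample size, the nominal power, the number of sites, or how strongly the strata predict either outcome.

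**The concern.** Stratified randomisation balances the arms within each combination of site and condition. The treatment contrast is then largely free of between-stratum variation. A regression that leaves the strata out does not use this, because it keeps that variation in the residual. If the strata are prognostic beyond the baseline score, the reported standard error exceeds the true one, the interval is too wide and the test rejects less often than 5% under the null.

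Two features of this plan give the point some weight. Both endpoints must succeed, so a loss on each compounds. The two co-primaries are also treated differently, because mobility has a planned strata-adjusted analysis and upright time has none.

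**Working it through.** The SAP states no power or sample size, so there is no figure of its own to reproduce. The check asks how large the loss could be.

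**Inputs from the SAP:** two-sided 5% (4.1); baseline score as the only covariate (4.1, 4.3, 4.4); both endpoints required (4.1).

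**Assumptions:** R² is the share of the variance left after the baseline score that the strata explain, taken from 0 to 0.20. Nominal power per endpoint is 80%, with 90% as an alternative. The strata are balanced between arms. A normal approximation is used.

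**Formulas.** Let ncp = 1.960 + 0.842 = 2.802, the expected test statistic on the scale of the baseline-only model's standard error at 80% power. With balanced strata, the true standard error is √(1−R²) times the one reported by that model. Hence:

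- excess of the reported standard error = 1/√(1−R²) − 1
- true type I error = 2[1 − Φ(1.960/√(1−R²))]
- power without strata = Φ((ncp − 1.960)/√(1−R²))
- power with strata = Φ(ncp/√(1−R²) − 1.960)

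**Example, R² = 0.10.** √0.90 = 0.949. The excess is 1/0.949 − 1 = 5.4%. Power without strata is Φ(0.842/0.949) = Φ(0.887) = 81.3%. Power with strata is Φ(2.802/0.949 − 1.960) = Φ(0.993) = 84.0%. The difference is 2.7 points.

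| R² | SE excess | True type I error | Power without strata | Power with strata | Loss (points) |
|---|---|---|---|---|---|
| 0 | 0% | 5.0% | 80.0% | 80.0% | 0 |
| 0.02 | 1.0% | 4.8% | 80.2% | 80.8% | 0.5 |
| 0.05 | 2.6% | 4.4% | 80.6% | 82.0% | 1.4 |
| 0.10 | 5.4% | 3.9% | 81.3% | 84.0% | 2.7 |
| 0.15 | 8.5% | 3.4% | 81.9% | 86.0% | 4.0 |
| 0.20 | 11.8% | 2.8% | 82.7% | 87.9% | 5.3 |

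Losses are taken before rounding. At 90% nominal power the loss runs from 0 to 2.8 points over the same range.

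**Both endpoints significant** (80% each, same R² for both). If the two test statistics are independent, joint power is the square of the single-endpoint power. It rises from 65.0% to 67.2% at R² = 0.05, from 66.0% to 70.5% at 0.10, and from 68.3% to 77.3% at 0.20. Positive correlation shrinks the gain. At R² = 0.10 it is 4.5 points under independence, 3.8 at an assumed correlation of 0.5, and 3.6 at 0.7.

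**Simulation** (assumed 300 participants, 6 strata, permuted blocks of 4, 5,000 runs per setting):

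| R² | Type I error without / with strata | Power without / with strata |
|---|---|---|
| 0 | 5.3% / 5.3% | 78.8% / 78.7% |
| 0.05 | 4.0% / 4.5% | 80.4% / 81.9% |
| 0.10 | 4.0% / 5.2% | 80.8% / 83.8% |
| 0.20 | 3.2% / 5.1% | 82.3% / 87.8% |

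At R² = 0.10 the baseline-only model reported a mean standard error of 0.116, while its estimates varied with a standard deviation of 0.109 to 0.112. The simulation agrees with the formulas within Monte Carlo error.

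**The case against.** A baseline-only analysis of covariance, fixed in advance, is a defensible primary analysis. The estimate is unbiased, and any departure from 5% is on the conservative side. For mobility, the strata-adjusted result is already planned, so the question there is only which of two models is called primary. The loss depends on an R² that the SAP does not give, and at 0.05 or below it is at most about 1.4 points per endpoint. The type I error figures are also idealised. The SAP does not describe block structure, missing outcomes are not imputed in the primary analysis (4.1), and upright-time data without enough wear time are excluded (section 3.1 and Appendix 2). The strata may therefore be less well balanced among those analysed.

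All of this stands, and it limits the point to efficiency. It does not explain why upright time lacks the analysis that mobility has. Nor does it favour leaving the strata out: if R² is near zero, adjusting costs little, and if it is not, precision is gained.

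Two stronger readings are tempting. A reader might infer that power is certainly lost on both endpoints. The document does not support this, because choosing a factor for stratification, or testing it as a subgroup, does not show that it predicts the outcome beyond baseline. A reader might also infer that the primary result is open to data-driven covariates, because 4.4 says: "Further adjusted analyses will be conducted if major imbalances between the groups at baseline are observed". That sentence comes after the primary model has been fixed as baseline-only and adds supplementary analyses. What counts as major is undefined, but this cannot change the primary result.

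**Conclusion.** The omission is documented for both co-primary endpoints, and 4.3 and 4.4 are inconsistent in what they plan for the strata. The direction of the effect is clear, but its size is conditional. Over an assumed R² of 0 to 0.20 and an assumed 80% nominal power, the standard error is 0 to 12% too large, true type I error runs from 5.0% down to 2.8%, and 0 to about 5 points of power are lost per endpoint. The loss is larger for the joint criterion, and most so among the cases considered if the endpoints are independent. These figures also assume that the strata remain balanced among those analysed. The point is a worthwhile improvement in efficiency and does not threaten the validity of the trial's conclusion.

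**What to change.** In SAP 4.1, 4.3 and 4.4, state one primary model for both co-primaries: 6-month score on group, baseline score, study site and neurological condition. In 4.3, say that the site and condition terms are kept if the change score is analysed. Report the baseline-only model for both endpoints as a sensitivity analysis.

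If the sponsor prefers to keep the baseline-only model as primary, the minimum is a sentence in 4.3 that plans the same strata-adjusted secondary analysis for upright time as 4.4 plans for mobility.

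The cost is a change of wording and a few degrees of freedom, depending on the number of sites, which the SAP does not state. No new data are needed, since both factors were used to randomise.

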## 4.5 Secondary outcomes

Physical Activity:

- The effect of group allocation on the continuous variable time spent upright (minutes per day averaged over days worn), assessed using the activPAL activity monitor at 3 week follow-up will be analysed using linear regression models with baseline scores entered into the linear regression models as covariates.
- The effect of group allocation on the continuous variable ‘average number of steps per day’ assessed using the activPAL activity monitor at 3 weeks and 6 months follow-up will be analysed using linear regression models with baseline scores entered into the linear regression models as covariates.
- average number of transitions per day’ at 3 weeks and 6 months follow-up will be analysed using linear regression models with baseline scores entered into the linear regression models as covariates.

Mobility:

- For this continuous secondary outcome, the groups will be compared on 3 week assessment CSPS, adjusted for baseline scores.
- A secondary analyses will be conducted using the 12-point scored version of the Short Physical Performance Battery^2^ and the sub-scores for the three test items: standing time with the feet in different positions (together, side by side, semi-tandem, tandem and single leg stance) (0-4), 4-metre walk (0-4), and repeated chair stand test (0-4). For these outcomes, the groups will be compared at 3 weeks and 6 months, adjusted for baseline scores.

For the other continuous secondary outcomes (see Appendix 1), the effect of group allocation at the specified time points cognition (3 weeks and 6months after randomisation), self-reported physical activity, activity performance and participation; quality of life, balance confidence and technology self-efficacy (3 and 12 weeks and 6 months after randomisation) will be analysed using linear regression models with baseline scores entered into the linear regression models as covariates. Or if distributions are overly skewed (on visual inspection of histograms) the change scores (post-pre) will be analysed. Mean between-group differences and their 95% CIs will be reported. In addition, self-reported measures of technology usability and enjoyment will be obtained from the intervention group (3 and 12 weeks and 6 months after randomisation).

Fall rates between groups will be compared using negative binomial regression. Interaction terms will be used in the models to assess whether effects of the intervention differed according to age or a neurological versus non-neurological health condition that affects daily activities.

